### Analysis for secondary endpoints

Important clinical covariates and sub-groups will be included in exploratory secondary analyses, and will include:DAH90DAH30ARISCAT scoreEURROSCORE IIGenderCOPDAsthmaObesity (BMI>35kg/m^2^)Current smoking statusLower respiratory tract infection in last 4 weeksAge (≤ or > 80 years)First time or re-do surgeryROX indexExtubation timing (≤ or >24 h after admission to ICU)Return to theatre (≤ or > 24 h of admission to ICU)Length of initial ICU stayCountryCentre (UK sites only)

#### Secondary outcomes

A series of Mann-Whitney-Wilcoxon tests will be used to assess whether a treatment effect exists for: DAH30; length of ICU stay during index admission; ROX index at 2, 6, 12, 24 and 48 h post-extubation; individual countries; and individual centres (UK only). Difference in medians with corresponding 95% confidence intervals will be reported for each comparison. The non-parametric confidence interval will be calculated using either the Hodges-Lehmann method if an exact p-value is available, or normal approximation otherwise.

Chi-squared tests (or Fisher’s exact test where appropriate) will be used to assess the association between the treatment group with extubation timing (≤ or >24 h after admission to ICU) and return to theatre (≤ or > 24 h of admission to ICU).

To allow for the estimation of effect sizes and adjustment for potential clinically important covariates, quantile regression models will be fitted for DAH90 and DAH30 as outlined in Table 2. Quantile regression was chosen due to the heavily skewed nature of the DAH endpoints and due to the expectation of two spikes close to day 0 and day 90/30.

**Table 2 Tab2:** Quantile regression models

Outcome variable	Explanatory variable(s)	Levels
DAH90	Treatment group	SOT [reference group], HFNT
DAH30	Treatment group	SOT [reference group], HFNT
DAH90	Treatment group ARISCAT risk category EUROSCORE II Gender COPD Asthma Obesity Current smoker Lower respiratory tract infection in last 4 weeks Age First time or re-do surgery Country	SOT [reference group], HFNT Low [reference group], intermediate, high - Female [reference group], Male No [reference group], Yes No [reference group], Yes No [reference group], Yes No [reference group], Yes No [reference group], Yes - First time [reference group], Re-do UK [reference group], Australia, New Zealand

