## Methods/design

### Design and setting

The study is an adaptive, multicentre, parallel-group, randomised controlled trial with embedded cost-effectiveness analysis comparing the use of HFNT to SOT for a minimum of 16 h after tracheal extubation, in patients at high risk of respiratory complications following cardiac surgery. Eligibility criteria and further details of the study design and setting are provided in the published study protocol [5]. Patients will be recruited from the UK, Australia and New Zealand. The NOTACS study includes an interim sample size re-estimation (SSR) which is expected to take place in late 2022, when a minimum of 300 patients have been randomised and followed up for 90 days.

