#### Interim analysis population

The interim analysis population will include all patients who have been recruited at the time 300 patients have completed 90 days follow-up, including patients with partial data (e.g. anyone recruited after the 300th patient who has not yet completed their follow-up, and anyone recruited before the 300th patient who left the trial before completing follow up). If there is greater than 15% missing data for DAH90 (excluding missingness because of death, which is informative) and the interim analysis is delayed because of that, the interim analysis population may include more than 300 patients. The trial will recruit from the UK, Australia and New Zealand. It is expected that the majority of the patients recruited by the end of the trial will be from UK centres. To ensure that the results of the interim SSR reflect the expected proportions of UK, Australian and New Zealand recruits, we will seek to ensure that between 50 and 75% of the patients included in the interim analysis are recruited from the UK, with the remainder from Australia and New Zealand. This will ensure that even if differences exist between the countries, the effect will not disproportionately bias the interim SSR and therefore will not affect the power at the end of the trial. This requirement may impact on the timing of the interim analysis and may require that more than 300 patients have been randomised and followed up to 90 days to achieve the proportions stated.

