### Analysis for the primary endpoint

The analysis of the primary and secondary endpoints will take place at the end of the trial following database lock.

The primary outcome is DAH90. Following the approach of Myles et al., for the primary analysis, DAH90 will be treated as 0 for any patient that dies in the period between randomisation and the 90-day follow-up [9]. This definition is deemed appropriate on the basis that the death rate in the trial population is expected to be low (around 3%), most deaths are expected to occur within the initial hospital admission, the death rate is expected to be comparable between the two treatment arms, and it is not expected that the treatment will impact on the death rate. The primary analysis will be on the basis of intention to treat (ITT).

Due to the skewed nature of DAH scores, a Mann-Whitney-Wilcoxon test will be used for the primary efficacy analysis. Contrasts between treatment groups for DAH90 will be used to evaluate the difference in the median DAH90 at a 5% significant level. 95% confidence intervals giving a range of plausible effects will be reported. The non-parametric confidence interval will be calculated using either the Hodges-Lehmann method if an exact p-value is available, or a normal approximation otherwise.

The statistical analysis will be reported according to CONSORT extension guidelines for reporting of adaptive trials [10]. A review statistician will independently reproduce the final primary efficacy analysis.

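### Separate tests within each country and each UK centre cannot show whether the treatment effect varies, and no analysis in the SAP article tests that

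*SAP article*

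**What the plan says.** The SAP article, under Analysis for secondary endpoints, subsection Secondary outcomes, opens: "A series of Mann-Whitney-Wilcoxon tests will be used to assess whether a treatment effect exists for". The list that follows mixes outcomes (DAH30, ICU stay, the ROX index at five times) with subgroups: "individual countries; and individual centres (UK only". No outcome is named for the country and centre tests. On reporting it says: "Difference in medians with corresponding 95% confidence intervals will be reported for each comparison".

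The parent section gives the status of this work: "Important clinical covariates and sub-groups will be included in exploratory secondary analyses", and its list includes country and, for UK sites, centre.

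In Table 2 the adjusted DAH90 quantile regression carries country as a covariate with levels "UK [reference group], Australia, New Zealand". No treatment-by-country term is listed, and centre is not in any of the models.

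The one efficacy test with a stated significance level is the primary analysis, which is to "evaluate the difference in the median DAH90 at a 5% significant level".

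**The concern.** A p-value within one country or centre asks whether the effect there is distinguishable from zero. Whether the effect differs between places is a separate question, and it needs a direct comparison of the effects. Significance in one place and none in another is what chance and unequal sample sizes produce even when the effect is identical everywhere.

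The article itself takes variation seriously. The sample size section says the nuisance parameters may differ between sites, and the interim population section allows for differences between countries. Yet the analysis chosen cannot say whether the treatment effect varies. At stake is how the site and country results are read: an isolated significant centre may be taken as a place where HFNT works, or a non-significant country as one where it does not.

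**Working it through.** **Inputs from the SAP article**
- Three countries: "Patients will be recruited from the UK, Australia and New Zealand".
- Sample size section: control median LOS 8 days; SD 12.85 (SOT) and 3.20 (HFNT); 3% deaths scored as LOS 90; LOS truncated at 90; a 2-day gain in median DAH90, so HFNT median LOS 8 − 2 = 6; crossover 12% from SOT and 25% from HFNT; 5% loss; total 310 unadjusted and 850 adjusted, each for 90% power.
- UK share: "between 50 and 75% of the patients included in the interim analysis are recruited from the UK". This is an interim target, applied here to the whole trial as an assumption.

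**Assumptions where the article is silent**
- 5 to 20 UK centres of equal size.
- Australia and New Zealand split the remainder equally.
- DAH90 is the outcome.
- Each test is two-sided at 5%, inferred from the 95% intervals.

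**Step 1. Reproduce the plan's own figures.** Lognormal log-SD s solves SD = median × √[(exp(s²) − 1) exp(s²)]. This gives s = 0.883 for SOT and 0.456 for HFNT. Crossovers draw from the other arm's distribution. With 30,000 simulated trials:
- N = 310, no crossover: power 89.9% with continuity correction and 90.3% without (stated 90%).
- N = 850 × 0.95 ≈ 807 analysed, with crossover: power 91.4% (stated 90%).

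Both agree with the plan, so the model can be used for smaller samples.

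**Step 2. Size of each single test.** With no effect, the rejection rate is 4.1% at 20 patients and 4.5% to 5.4% at 30 to 100. Small samples do not inflate it.

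**Step 3. Chance of at least one p<0.05 with no effect anywhere.** With k UK centres there are 3 + k tests. If they were independent, the chance would be 1 − 0.95^(3+k). The UK test and the UK centre tests share patients, so a nested simulation is the better figure (2,000 replicates per setting, Monte Carlo standard error about 1 point).

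| UK centres | Patients per centre (UK share 50% to 75% of 807) | Tests | Independence formula | Nested simulation |
|---|---|---|---|---|
| 5 | 80–120 | 8 | 34% | 30% |
| 10 | 40–60 | 13 | 49% | 46–47% |
| 15 | 26–40 | 18 | 60% | 56–57% |
| 20 | 20–30 | 23 | 69% | 65–66% |

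The chance passes 50% only somewhere between 10 and 15 centres.

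**Step 4. What a centre result shows if the planned effect holds everywhere.** Wrong direction means that the rank statistic favours SOT.

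| Patients in centre | Power | Wrong direction |
|---|---|---|
| 20 | 7% | 30% |
| 40 | 11% | 23% |
| 60 | 14% | 18% |
| 106 | 23% | 11% |

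For example, with 10 centres of 40, about 10 × 0.11 = 1.1 would be significant and 10 × 0.23 = 2.3 would favour SOT, although the true effect is the same in all ten. A centre of 120, the largest in the first table, lies between the 23% at 106 and the 31% found at 150.

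**Step 5. Countries.** The UK would have 0.50 × 850 = 425 to 0.75 × 850 ≈ 638 patients, with power of about 66% to 85%. Australia and New Zealand would each have about 106 (UK share 75%) to 212 (UK share 50%), with power of 23% to 40%. A significant UK result beside two non-significant ones could therefore easily arise under a common effect.

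**Step 6. The alternative.** One country and one centre heterogeneity test make two tests. The chance of any false positive is at most 10%, or 1 − 0.95² = 9.75% if they are independent.

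**The case against.** The strongest reply is that these analyses are openly exploratory. They do not touch the primary comparison or its 5% level, and error control across exploratory comparisons is a weak ground for complaint. The article announces no claim about individual sites, so any over-reading would be a reporting fault. It already promises an estimate and interval for each comparison, which is most of what a descriptive display needs. All of this stands, and it keeps the point minor. It does not make a within-centre p-value an answer to the heterogeneity question, and the article still frames each test as asking whether an effect exists.

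A reader might also infer three stronger things that the document does not support:
- That small centres cause false positives. Step 2 shows they do not; the number of tests does. Small centres bring low power and reversed directions.
- That all the subgroups are tiny. The UK as a whole would hold half or more of the trial under the assumed share.
- That a false positive is likely. That depends on a centre count the article does not give; at 5 centres the chance is about 30%.

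Finally, the article condenses a fuller SAP and refers to an additional document. The paragraph on these tests does not defer to it, so this is only a small caution.

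**Conclusion.** The point holds as a matter of method and is minor in weight. The article fixes separate tests by country and by UK centre, and nothing it shows tests whether the effect varies.

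The family-wise figures (about 30% to 65%) rest on the assumed 5 to 20 equal centres, DAH90 as the outcome and two-sided 5% tests. If more outcomes were tested by place, the number of tests would rise. The within-centre power (about 7% to 23% at 20 to 106 patients) and the wrong-direction rates (about 30% to 11%) rest on the plan's own distributional model, which reproduces its stated power. That separate p-values do not measure heterogeneity depends on none of these assumptions. The primary conclusion and its type I error are unaffected.

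**What to change.** In the Secondary outcomes subsection and Table 2:
1. Name DAH90 as the outcome for the country and centre analyses.
2. Remove the per-country and per-centre p-values.
3. Add a treatment-by-country interaction to the adjusted DAH90 quantile regression. Country has three levels, so this takes two coefficients, tested jointly.
4. Add one heterogeneity test across UK centres, for example across centre-stratified rank statistics. The country interaction says nothing about differences between UK centres, so both are needed.
5. Show the already planned country and centre estimates with 95% intervals in a forest plot, described as descriptive.

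The cost is SAP wording and a little extra modelling, with no change to data collection or sample size. The downside is that both heterogeneity tests will have low power, so a non-significant result must not be read as evidence that the effect is uniform.

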### Sensitivity analyses

A number of sensitivity analyses will be performed to examine the robustness of the primary analysis. These include:Using the per-protocol population instead of the ITT population;Using each of the two ToT populations instead of the ITT population;Using an alternative definition of DAH90 for patients that die during follow-up;Examination of missing data, with multiple imputation of missing data where appropriate.

Further details of these sensitivity analyses can be found in the additional document.

### Safety analyses

All safety analyses will be performed on the safety population. Data on AEs and SAEs will be collected from the time of tracheal extubation to discharge. From discharge up to 90 days after surgery, only data on SAEs will be collected. Adverse events (AEs) and serious adverse events (SAEs) will be summarised separately. AE and SAE data will be listed by MedDRA Preferred Term and further grouped by System Organ Class. The frequencies of the AEs will be summarised by treatment groups. Death, stroke, sepsis, myocardial infarction and acute kidney injury are SAEs of special interest. Therefore, the rates of these will be estimated for each treatment group separately to the main SAE summary table.

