### Objectives

The primary objectives are to determine if prophylactic use of HFNT (for a minimum of 16 h after tracheal extubation) is clinically and cost-effectively superior in comparison with standard oxygen therapy (SOT) up to 90 days after surgery, for adult patients undergoing cardiac procedures with cardiopulmonary bypass who are at high risk of postoperative pulmonary complications. The primary objective around clinical efficacy will be evaluated by comparing DAH90 (days alive and at home in the first 90 days after the planned surgery) between the two treatment arms.

The secondary objectives are to determine if prophylactic use of HFNT is able to:Reduce mortality, pulmonary complications, intensive care re-admission rate, length of hospital and intensive care stay.Reduce incidence of major complications including sepsis, acute kidney injury, myocardial infarction and stroke.Reduce readmission to hospital rate.Improve oxygenation as measured by the ROX Index.Improve patient-centred outcomes as measured using the EQ-5D-5L.Reduce patient level of assistance needed with activities of daily living as measured using BARTHEL questionnaire.Improve quality of survival as measured using ED-5D-5L quality-adjusted life years.Reduce health service and resource use.

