### Secondary outcomes

The secondary outcomes include:DAH30 (days alive and at home in the first 30 days after the planned surgery)Incidence of adverse events and serious adverse events (including death)Incidence of stroke, sepsis, acute kidney injury and myocardial infarctionPostoperative pulmonary complicationsICU re-admission rate during index admissionTotal length of ICU stay (days) during index admissionTotal length of hospital stay (days) during index admissionRe-admission to hospitalOxygenation, as measured by ROX IndexPatient-reported outcomes (EQ-5D-5L)Patient level of assistance needed with Activities of Daily Living (BARTHEL questionnaire)Quality of survival (QALYs)Health service and resource use

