#### Safety population

The safety population includes all subjects entered into the trial from the time of tracheal extubation up to 90 days after surgery (the period for which safety data is being collected) at the time of database lock. The safety population will be used to provide summary statistics on adverse events (AEs) and serious adverse events (SAEs), which will be reported by the treatment arm assigned during randomisation (or by the treatment arm actually received if it is different to that assigned during randomisation). The safety population will be examined at both the interim and final analyses. It will include patients with partial data as well as any patients who have withdrawn from the trial provided they continue to consent to their data being used.

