#### Intention-to-treat population

The ITT population is the population that will be used for the majority of the analyses, including the analysis of the primary endpoint and the interim sample size re-estimation. The ITT population includes all subjects who were randomised, regardless of whether they received the treatment randomly allocated to them or completed follow-up. The data will be analysed assuming that the patient received the treatment they were randomly allocated to. If a patient dies after being randomised but before extubation occurs, they will be included in the ITT analysis population with a days at home score of zero.

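### The only stated mortality analysis counts deaths from extubation and by treatment received, while DAH90 counts them from randomisation and by allocated arm

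*SAP article*

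**What the plan says.** The SAP article handles death in two places, under different rules.

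**In the primary endpoint.** Under Analysis for the primary endpoint, "DAH90 will be treated as 0 for any patient that dies in the period between randomisation and the 90-day follow-up". The Intention-to-treat population section covers the early deaths explicitly and assigns them zero: "If a patient dies after being randomised but before extubation occurs, they will be included in the ITT analysis population with a days at home" (the value given there is 0). Patients are analysed in the arm to which they were allocated.

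**As an outcome in its own right.** Mortality comes first in the list of secondary objectives: "Reduce mortality, pulmonary complications, intensive care re-admission rate". Under Secondary outcomes it has no line of its own and appears only within "Incidence of adverse events and serious adverse events (including death"). Safety analyses then states how it is analysed:

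- "Death, stroke, sepsis, myocardial infarction and acute kidney injury are SAEs of special interest", with a rate to be estimated for each treatment group.
- The population is named: "All safety analyses will be performed on the safety population".
- The collection window opens at extubation: "Data on AEs and SAEs will be collected from the time of tracheal extubation to discharge". After that, and until 90 days after surgery, only SAEs are collected.

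The Safety population section gives the same window, "from the time of tracheal extubation up to 90 days after surgery (the period for which safety data is being collected"). It reports a patient under the treatment actually received when that is not the one assigned.

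The tests listed under Analysis for secondary endpoints do not include mortality. The overall death rate re-estimated at the interim sample size re-estimation is a nuisance parameter, not a comparison between arms.

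**The concern.** The two rules differ in both start point and grouping. A randomised patient who dies before extubation is a death for DAH90 but falls outside the window of the mortality rate. A patient who crosses over may be counted in one arm for DAH90 and in the other for mortality.

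Three things are at stake:

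- The mortality objective concerns a benefit of the allocated strategy. The stated analysis answers it neither from randomisation nor by allocation, and it can understate 90-day mortality among the randomised patients.
- The deaths behind the DAH90 zeros and the deaths in the mortality table need not agree, and no reconciliation is stated.
- Analysis for the primary endpoint justifies scoring death as zero partly because death rates should be low, similar in the two arms and unaffected by treatment. A table with a later start and a different grouping cannot check that premise for the deaths that DAH90 actually uses.

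**Working it through.** **1. The rules side by side**

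| | DAH90 | Stated mortality rate |
|---|---|---|
| Population | ITT, all randomised | Safety population |
| Counting starts | Randomisation | Tracheal extubation |
| Counting ends | 90-day follow-up | 90 days after surgery |
| Grouping | Allocated arm | Treatment received, if different from assigned |
| Death before extubation | Counted, score 0 | Outside the window |

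The ITT definition provides for deaths before extubation, so the plan itself foresees the case.

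**2. The plan's own figures**

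The Sample size calculation section gives a 3% death rate, 310 patients unadjusted and 850 after crossover and loss, at 90% power. A simulation of 4,000 replicates per scenario used:

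- lognormal length of stay, with median 8 and SD 12.85 in control, and median 6 (8 − 2) and SD 3.20 in treatment;
- truncation at 90 days and 3% deaths;
- a two-sided 5% Mann-Whitney-Wilcoxon test (two-sided is an assumption).

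It gave 90.2% power at 310, and 91.4% at 850 with 12% and 25% crossover and 5% loss. The stated sizes therefore reproduce. This only checks the inputs: DAH90 already contains the deaths in question, so the sample size does not change.

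**3. Deaths left out of the mortality rate**

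Expected deaths = N × 0.03, which is 25.5 at 850 and 34.56 at the maximum of 1152. The document does not give the share *s* that falls between randomisation and extubation, so *s* is an assumption shown over a range.

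Omitted deaths = N × 0.03 × *s*. Reported rate = 0.03 × (1 − *s*).

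| Assumed *s* | Omitted, N = 850 | Omitted, N = 1152 | Reported rate |
|---|---|---|---|
| 5% | 1.28 | 1.73 | 2.85% |
| 10% | 2.55 | 3.46 | 2.70% |
| 20% | 5.10 | 6.91 | 2.40% |
| 30% | 7.65 | 10.37 | 2.10% |

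If these patients also leave the denominator, the rate is 0.03(1 − *s*)/(1 − 0.03*s*): 2.85%, 2.71%, 2.41% and 2.12%. The choice of denominator hardly matters.

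**4. Patients who may change arm**

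With 425 per arm, planned crossover is 0.12 × 425 = 51 from SOT and 0.25 × 425 = 106.25 from HFNT. Together that is 157.25 of 850, or 18.5%. This is the number regrouped if every crossover counts as having received the other treatment. The article does not say when a switch counts as such, so the number could be lower.

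**The case against.** The strongest reply is that this is a condensed article. It lists hospital length of stay, re-admission, pulmonary complications, EQ-5D-5L and Barthel as secondary outcomes and prints no test for them either. It also defers derived variables, further populations and other summaries to an additional document, which could contain an ITT mortality summary. That stands as a limit: the article does not prove that no such summary exists. It does not remove the point, because for mortality the article is not silent. It states a rule, and that rule uses a different window and grouping from the primary endpoint.

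A second reply is that a safety window opening at extubation is natural when the allocated therapy starts there, and that the safety population wording may describe the data period without excluding patients who were never extubated. Both are fair. The window suits AEs and SAEs in general. It does not suit a mortality objective for randomised patients, and SAE collection still opens at extubation on either reading.

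A reader might also infer more than the text supports:

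- **That unblinded staff select who enters the mortality comparison.** Randomisation and blinding says staff cannot be blinded while the patient receives randomised therapy. It does not say that allocation is known when extubation is decided. Differential selection is not shown.
- **That the DMEC or readers cannot separate deaths from other zeros.** Deaths are identified elsewhere: in the interim overall death rate, in the interim missing-data rule that sets death apart, and in the sensitivity analysis that redefines DAH90 for patients who die.
- **That many deaths are lost, for example in theatre.** The article does not give the time of randomisation relative to surgery. It expects most deaths in the initial admission, which continues past extubation, and so gives no pre-extubation share.

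**Conclusion.** The point holds as a mismatch between stated rules. As written, the mortality rate omits deaths between randomisation and extubation that DAH90 scores as zero. It is also not an ITT comparison wherever treatment received replaces allocation.

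Its size rests on two assumptions: the plan's 3% death rate, and a pre-extubation share of 5% to 30% that has no source in the document. On these, about 1 to 8 of 25.5 deaths are omitted at 850 patients, or about 2 to 10 of 34.56 at 1152. The true number may be at or below the low end. Bias between arms is possible but not demonstrated.

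The primary analysis and the sample size are unaffected. The change should still be made, because mortality is a named objective, events are few, and the remedy is cheap.

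**What to change.** For the mortality objective, add to Secondary outcomes and to Analysis for secondary endpoints: all-cause death from randomisation to day 90 after surgery, in the ITT population by allocated arm, reported as numbers and rates with a risk difference and 95% CI. Require the total to be reconciled with the number of DAH90 values set to zero because of death, leaving aside any zeros in survivors.

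Keep the from-extubation table in the safety population for AEs and SAEs, and label its window and grouping so that readers can see why its death count may differ. If the additional document already contains such a mortality analysis, a sentence pointing to it is enough.

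The cost is SAP wording and one extra table line. No new data are needed, because scoring DAH90 already requires every death from randomisation to be known. The one drawback is that two death figures will appear in the report, which the labelling and reconciliation deal with.

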A total sample size of 310 has 90% power to detect an increase of 2 days in the median DAH90 using the Mann-Whitney-Wilcoxon test for the analysis. After adjustment for 12% crossover from standard oxygen to HFNT and 25% crossover from HFNT to standard oxygen as well as an extra 5% loss to follow-up (equally distributed among arms), the total sample size needed to detect a 2-day increase in DAH90 with 90% power with an intention-to-treat (ITT) analysis is 850 patients.

The minimum target sample size (based on initial assumptions) is 850 randomised participants. The final sample size target will be revisited after a minimum of 300 patients have been randomised and followed up to 90 days. The adaptive design will allow for a maximum sample size increase to 1152 patients. In the event that the interim analysis recommends a sample size less than 850, recruitment will continue to the original minimum target sample size of 850.

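### Non-serious AEs are counted only to discharge and tabulated as crude frequencies, so the arms may be observed for unequal lengths of time; the size is unknown, and a fixed early window would address it

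*SAP article*

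**What the plan says.** The Safety analyses section sets two collection periods. For the hospital stay, "Data on AEs and SAEs will be collected from the time of tracheal extubation to discharge". After that, "From discharge up to 90 days after surgery, only data on SAEs will be collected". The reporting rule is "The frequencies of the AEs will be summarised by treatment groups". The section gives no common cut-off day, no person-time denominator and no test, and it does not refer the reader to the additional document.

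It also states that "Death, stroke, sepsis, myocardial infarction and acute kidney injury are SAEs of special interest", with their rates reported separately. The Safety population section reports events by the assigned arm, "or by the treatment arm actually received if it is different to that assigned during randomisation".

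Three other places matter:
- Secondary outcomes lists the incidence of AEs and SAEs.
- Objectives includes "Reduce mortality, pulmonary complications, intensive care re-admission rate, length of hospital and intensive care stay".
- Interim analysis makes the interim safety analyses identical to the final ones.

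**The concern.** The window for non-serious AEs closes at discharge, and earlier discharge is what the trial hopes HFNT will achieve. In the Sample size calculation, DAH90 is 90 minus length of stay, so the 2-day target gain is a 2-day shorter stay. If the hypothesis is true, HFNT patients are watched for non-serious AEs for less time, and the treatment itself causes the difference. Two arms with the same underlying AE hazard could then show different frequencies, probably fewer on HFNT.

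At stake is how a listed secondary outcome is read, at the final analysis and by the monitoring committee at the interim. The primary analysis is not touched.

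**Working it through.** **Inputs (Sample size calculation).** Control median stay 8 days; SD 12.85 (SOT) and 3.20 (HFNT); lognormal stay truncated at 90; 3% deaths scored as 90; 2-day shift in the median; switching 12% (SOT to HFNT) and 25% (HFNT to SOT); 5% loss. The HFNT median of 6 is not printed; it follows as 8 − 2.

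**1. Reproduce the plan's own figures.** The plan states: "A total sample size of 310 has 90% power to detect an increase of 2 days in the median DAH90 using the Mann-Whitney-Wilcoxon test". Simulating that model with a two-sided 5% Mann-Whitney-Wilcoxon test (10,000 replicates) gives power 0.905 at N = 310, or 0.910 with stays rounded to whole days. With switching and 850 × 0.95 ≈ 808 evaluable patients, power is 0.914 (0.915 rounded). Both agree with the stated 90% to within 2 points, so the model is a fair reading of the plan.

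**2. Length of the AE window.** For a lognormal with median m and SD s, put w = [1 + √(1 + 4(s/m)²)]/2; the mean is m√w.
- SOT: w = 2.182, mean 8 × 1.477 = 11.8, or 11.7 after truncation at 90.
- HFNT: w = 1.231, mean 6 × 1.110 = 6.7.
- Ratio of means 6.7/11.7 = 0.57; ratio of medians 6/8 = 0.75.
- After switching: SOT 0.88 × 11.7 + 0.12 × 6.7 = 11.1; HFNT 0.75 × 6.7 + 0.25 × 11.7 = 7.9; ratio 0.71. Medians are 7.6 and 6.3.

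Deaths are left out here. Stay is taken as the window although AE collection starts at extubation; starting there shortens both windows and widens the relative gap slightly.

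**3. Apparent AE ratio when the true hazards are equal.** The article gives no AE rate or timing, so the hazard shape is an assumption shown as a range. Expected AEs per patient are proportional to E[L] for a constant hazard, and to E[(1 − e^(−λL))/λ] with λ = ln 2/h for a hazard that halves every h days. The per-patient-day ratio is the count ratio divided by the ratio of mean stays (for example 0.88/0.57 = 1.54). The true ratio is 1.00 throughout.

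| Hazard after extubation | Crude count ratio, full adherence | Crude, after switching | Per patient-day, full adherence | Per patient-day, after switching |
|---|---|---|---|---|
| Constant | 0.57 | 0.71 | 1.00 | 1.00 |
| Half-life 5 days | 0.88 | 0.92 | 1.54 | 1.29 |
| Half-life 3 days | 0.95 | 0.97 | 1.67 | 1.36 |
| Half-life 2 days | 0.99 | 0.99 | 1.74 | 1.39 |
| Half-life 1 day | 1.02 | 1.01 | 1.79 | 1.42 |

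For the proportion of patients with any AE, the constant hazard turns 50% on SOT into 40% on HFNT (44% after switching), and 30% into 21% (24%).

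**4. Dependence on the SDs.** If HFNT had SD 12.85 as well, the constant-hazard count ratio would be 0.83 (0.89 after switching), and 0.88 to 0.96 (0.92 to 0.97) for half-lives of 5 to 1 days.

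**5. A fixed early window.** Counting only in-hospital AEs up to day 2, 3, 4 or 5 with the stated SDs, the ratio lies between 1.01 and 1.04 under every hazard above, and slightly nearer 1 after switching. At day 3, 87% of SOT and 94% of HFNT patients are still in hospital; at day 5, 70% and 66%. With SD 12.85 in both arms the ratio is 0.97 to 0.98 for a 2-day window and falls to 0.91 for a 5-day window with a constant hazard, so a shorter window is safer.

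**The case against.** The strongest reply is that the crude table may be nearly right. Randomised therapy runs for a minimum of 16 hours after extubation, and planned median stays are 6 and 8 days, so most patients are in hospital throughout the early period in both arms. If AEs cluster there, the table is off by about 1% to 2% and can even lean the other way. This stands.

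A reader might infer that HFNT would look 29% to 43% safer (1 − 0.71 and 1 − 0.57). The documents do not support that as an expected size. It needs a constant daily hazard, it applies to counts rather than to the proportion affected, and much of it comes from the SDs of 12.85 and 3.20, which the SAP itself treats as uncertain and will re-estimate.

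A reader might also infer that the plan could hide serious harm or that a formal comparison is biased. Neither follows. SAEs run to day 90 in both arms, the five events of special interest get their own rates, no test is stated for AEs, and unequal stay will be visible because length of hospital stay is an outcome.

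The obvious remedy, AEs per patient-day, can be worse than the problem. With a declining hazard, the long, quiet late stays on SOT dilute its rate, and equal hazards show as a 29% to 79% excess on HFNT.

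Finally, a fuller SAP exists and may tabulate AEs by time. That cannot be seen, but the rule printed in the Safety analyses section is explicit. What remains is that it ends observation at an event the treatment is meant to change.

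**Conclusion.** The point holds as a reporting weakness in the non-serious AE table. If the trial's hypothesis about stay is right, the arms will be observed for different lengths of time and the crude frequencies may tend to favour HFNT. Under the planning distributions and equal true hazards, the count ratio could lie anywhere from about 0.57 (0.71 after switching) to about 1.0. The position in that range depends on AE timing, which the article does not give, and on the HFNT SD. Because safety tables may place switchers in the arm received, the full-adherence figures may be the nearer ones.

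The 90-day SAE tables and the primary analysis are unaffected. This is a cheap improvement to make before the data are seen, not a flaw that undermines the trial's safety assessment.

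**What to change.** - Keep the crude AE table, and state beside it that collection ends at discharge, with the observed length of the window in each arm.
- Pre-specify a summary of AEs by arm within a fixed number of days after extubation, short enough that most patients in both arms are still in hospital, and show how many were discharged before the window ended.
- Base between-arm safety statements on that table and on SAEs to 90 days, at both the interim and the final analysis.
- Do not base them on AEs per patient-day.

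The cost is one extra table. It needs no change to care or to the collection period. It assumes that AE onset dates are recorded, which the article does not state; index stay is already an outcome. The downside is that the new table leaves out later in-hospital AEs, which then appear only in the crude table. Some imbalance also remains from patients discharged inside the window, which is why their number should be shown.
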